| Control Group                    | Continuation of HF Medications                                                                                                                                                                                                                                                                                                                                                                                                                                                                                                                                                                             |
| Methods                          | Patients who have signed the Institutional Review Board (IRB) / Ethics Committee (EC)-approved Informed Consent Form (ICF) and are judged by the investigator to meet all inclusion and exclusion criteria will be enrolled into the study. Following enrollment, subjects will be randomized in a 1:1 ratio to either the intervention group or the control group. The intervention group will undergo stepwise withdrawal of HF medications, while the control group will continue the HF medications. Patients will be followed for 6 months to compare the efficacy and safety between the two groups. |
| Sample Size                      | This study requires the enrollment of 50 patients, with 25 patients allocated to each group.                                                                                                                                                                                                                                                                                                                                                                                                                                                                                                               |

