#### **4.3.2 Secondary Endpoints**

- (1) Composite of cardiovascular death, hospitalization for HF, non-fatal stroke, or non-fatal myocardial infarction;
- (2) Changes from baseline to 6 months in the following parameters:
  - a) Echocardiography: LVEF, LVEDD;
  - b) Cardiac magnetic resonance (CMR): LVEF, left ventricular end-diastolic volume index (LVEDVi), left ventricular global longitudinal strain (LV-GLS), and percentage of late gadolinium enhancement (LGE);
  - c) NT-proBNP;
  - d) KCCQ-12 score;
  - e) Heart rate;
  - f) Systolic blood pressure;
  - g) Diastolic blood pressure.
- (3) Recurrence of atrial tachyarrhythmia and atrial tachyarrhythmia burden;
- (4) Adverse drug events, including symptomatic hypotension, renal dysfunction, hyperkalemia, bradycardia, diabetic ketoacidosis and urogenital infection.

Definitions: 1) renal dysfunction: a decrease in the eGFR of  $\geq 50\%$  or a decrease of  $>30$  mL/min/1.73 m^2 from randomization to  $<60$  mL/min/1.73 m^2; 2) hyperkalemia: serum potassium  $>5.5$  mmol/L; and 3) bradycardia: heart rate at rest  $<40$  beats/min.

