##### **4.4.1 Stepwise GDMT Withdrawal Group Protocol:**

medications were reduced or discontinued stepwise every 2 weeks, with one medication adjusted at a time. For patients on  $>20$  mg spironolactone,  $>10$  mg finerenone,  $>40$  mg furosemide, or  $>25\%$  of ARNi/RASi or beta-blockers target doses, dosages were reduced by

50% every two weeks. Medication doses at or below these thresholds and SGLT2 inhibitors, were discontinued immediately. The withdrawal sequence was: loop diuretics, MRAs, beta-blockers, ARNi/RASi, and SGLT2 inhibitors. GDMT was reinitiated if the primary endpoint occurred.

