##### **4.5.2.3 Visit 3-7 (Monthly Follow-up)**

Participants will monitor blood pressure and heart rate daily. Monthly assessments will include NT-proBNP, liver and renal function tests with electrolytes, urinalysis, echocardiography, and 24-hour Holter ECG. At 6 months, CMR will be repeated along with KCCQ questionnaire evaluation. Echocardiography and 24-hour Holter ECG will also be performed, and current medication use will be recorded monthly.

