## **5. Statistical Methods**

### **5.1 Sample Size Calculation**

This study is designed to explore the feasibility of a future large-scale trial. The sample size is set at 50 participants, based on a 2019 Lancet study investigating withdrawal of HF medications in patients with dilated cardiomyopathy.

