### **5.3.2 General Principles**

**Descriptive Statistics:** For quantitative variables, the number of observations, mean, standard deviation, median, interquartile range, minimum, and maximum will be reported. For categorical variables, counts and percentages for each category will be presented.

**Inferential Statistics:** Unless otherwise specified, all statistical tests will be two-sided, and a P-value  $\leq 0.05$  (two-sided) will be considered statistically significant. The primary endpoint was compared using the chi-squared or Fisher's exact test. Secondary endpoints were compared using Wilcoxon rank-sum test for continuous variables, and chi-squared or Fisher's exact test for categorical variables.

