## **5.4 Handling of Missing and Aberrant Data**

A statistical analysis plan will be developed before the trial begins. After database lock, statistical analyses will be conducted according to the plan, and a statistical analysis report will be generated based on the results.

**5.4.1 Handling of Missing Data:** Missing data will not be imputed; analyses will be performed using the available data.

**5.4.2 Handling of Erroneous Data:** During data management, quality control will be performed on the database. Identified erroneous data will be queried to the investigators via a data query form. Corrections will be made based on the investigators' written responses. The database will only be locked after all erroneous data have been corrected.

**5.4.3 Handling of Implausible Data:** During data management, logical checks will be performed on the database. Implausible data will be queried to the investigators via a data query form. Adjustments will be made based on the investigators' written responses. The database will only be locked after all implausible data have been resolved.

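### The change-from-baseline secondary endpoints are compared by a Wilcoxon test without baseline as a covariate and without a between-arm estimate: valid, but less precise and less useful for planning than the data allow

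*Protocol*

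**What the plan says.** - **Method.** Section 5.3.2: "Secondary endpoints were compared using Wilcoxon rank-sum test for continuous variables". No covariate, model or between-arm estimate is named. The same section sets the general rule that "all statistical tests will be two-sided, and a P-value" of at most 0.05 counts as significant, and plans descriptive statistics for quantitative variables.
- **Endpoints.** Section 4.3.2 lists "Changes from baseline to 6 months in the following parameters": echo LVEF and LVEDD; CMR LVEF, LVEDVi, LV-GLS and percentage of LGE; NT-proBNP; KCCQ-12; heart rate; systolic and diastolic blood pressure. That is eleven variables.
- **Schedule.** Section 4.5.2.3: "Monthly assessments will include NT-proBNP, liver and renal function tests with electrolytes, urinalysis, echocardiography, and 24-hour Holter ECG". The flowchart in 4.5.1 marks vital signs at every visit. CMR and KCCQ are taken only at screening and month 6. Interim readings therefore exist for six of the eleven variables.
- **Size.** Section 5.1: "The sample size is set at 50 participants, based on a 2019 Lancet study". The Protocol Summary adds "with 25 patients allocated to each group".
- **Missing data.** Section 5.4.1: "Missing data will not be imputed; analyses will be performed using the available data".
- **Restart of treatment.** Section 4.4.1, for the withdrawal arm: "GDMT was reinitiated if the primary endpoint occurred". Under section 4.7.1, all randomized patients not lost to follow-up are analysed in their assigned arm. The protocol does not say how values after restart are to be treated.

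**The concern.** Each of the eleven variables has a baseline value. Subtracting it is not the same as adjusting for it. Unless baseline and month-6 values are very highly correlated, the change score carries baseline noise that regression on baseline would remove. With 25 patients per arm, that loss counts.

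The output matters too. Sections 4.1 and 5.1 say the trial exists to judge whether a larger one is feasible. A rank-sum P-value gives no size of difference and no interval, and those are what a later sample size calculation uses.

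A separate question is what the month-6 contrast means. A withdrawal-arm patient who deteriorates goes back on treatment and may have partly or fully recovered by month 6. That value then enters the comparison like any other.

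**Working it through.** The protocol gives no SD, effect size, power or correlation, so there is no figure of its own to reproduce. The correlation rho between baseline and month 6, the relapse share and the recovery are assumptions, shown as ranges.

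**1. Precision with equal SDs (set to 1).** Variance of the change score: 2(1 − rho). Residual variance under ANCOVA: 1 − rho². Ratio ANCOVA/change: (1 + rho)/2. The gain in patients is the inverse minus 1. The last column multiplies 50(1 + rho)/2 by 0.955, the efficiency of the Wilcoxon test relative to the t-test under normality.

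| rho | ratio | gain from ANCOVA | 50 patients under Wilcoxon on change equal, under ANCOVA |
|---|---|---|---|
| 0.3 | 0.65 | 54% | 31.0 |
| 0.5 | 0.75 | 33% | 35.8 |
| 0.7 | 0.85 | 18% | 40.6 |

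Simulation with 25 per arm, 3,000 runs and a 0.8 SD shift gave this power for Wilcoxon on change against ANCOVA: 61.8% v 81.8% (rho 0.3), 77.0% v 88.8% (0.5), 93.5% v 97.3% (0.7). With no true difference, Wilcoxon rejected in 4.7% to 5.0% of runs over rho 0.3 to 0.8, so type I error is sound.

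**2. Variables truncated at entry.** Section 4.2.1 requires LVEF of at least 55%, LVEDD in the normal range and NT-proBNP below 250 ng/L. Selecting on baseline leaves the regression slope b (here equal to the unrestricted rho) and the residual variance 1 − rho² unchanged, but shrinks the baseline variance V. Then

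Var(change) = (1 − rho²) + (1 − b)² × V.

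As an illustration, keep only the upper half of a normal baseline (by symmetry, the lower half for LVEDD and NT-proBNP): V = 1 − 2/π = 0.363, SD 0.60.

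| unrestricted rho | Var(change) | ANCOVA variance | gain |
|---|---|---|---|
| 0.3 | 0.91 + 0.49 × 0.363 = 1.088 | 0.91 | 20% |
| 0.5 | 0.75 + 0.25 × 0.363 = 0.841 | 0.75 | 12% |
| 0.7 | 0.51 + 0.09 × 0.363 = 0.543 | 0.51 | 6% |

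The entry cut-offs therefore reduce the gain for these three variables.

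**3. Interim readings.** With complete data, a repeated-measures model gives essentially the ANCOVA contrast at month 6. The monthly values help mainly a retained patient whose month-6 reading is missing. The protocol gives no rate for this.

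**4. Values after restart.** Suppose 5 of 25 withdrawal patients fall by 12 LVEF points and restart. Their contribution to the arm mean is 5/25 × 12 = 2.4 points with no recovery by month 6, 1.2 with half recovery and 0 with full recovery. A simulation with 40% relapse, a 2 SD drop and rho 0.5 shows the same pattern:

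| recovery by month 6 | mean difference | Wilcoxon power | ANCOVA power |
|---|---|---|---|
| none | 0.8 SD | 54% | 72% |
| half | 0.4 SD | 24% | 31% |
| full | 0 | 5% | 5% |

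With 20% relapse, Wilcoxon power is 17% with no recovery and 8% with half recovery. Baseline adjustment does not remove the dilution.

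**The case against.** The strongest reply is that covariates, intervals and sensitivity analyses usually belong in the statistical analysis plan, which section 5.4 promises and which is not shown. That holds for details left open. It does not hold for the test, which section 5.3.2 names. The opening qualifier there attaches to sidedness and significance level, not to the choice of Wilcoxon.

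It is also fair that these are secondary endpoints of a pilot, that the test is valid, and that the planned means, SDs and quartiles by arm already give some planning input. This limits the weight of the point. It does not supply a difference with an interval.

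A reader might infer more than the documents support:

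- *That baseline is ignored.* It is subtracted; it is only not a covariate.
- *That five monthly readings are discarded throughout.* They exist for six of eleven variables, not for CMR or KCCQ-12.
- *That the narrow entry range makes adjustment more valuable.* Step 2 shows the opposite.
- *That the trial hides deterioration.* Section 4.3.1 counts a qualifying deterioration at any time within 6 months, so a patient who relapses and recovers is still a primary event. Keeping values after restart in the assigned arm is a recognised treatment-policy approach. What is missing is a statement that this is intended.
- *That a repeated-measures model would recover patients lost to follow-up.* The modified intention-to-treat set excludes them whatever the model.

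**Conclusion.** The point holds as one of precision and reporting, not of validity. Under equal SDs and rho 0.3 to 0.7, the unadjusted change analysis forgoes what 54% to 18% more patients would give. For echo LVEF, LVEDD and NT-proBNP the figure is nearer 20% to 6%, if entry keeps about half of the baseline range. All of these rest on assumed correlations and, for the truncated variables, on an assumed degree of narrowing.

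Dilution by values after restart is a real mechanism under sections 4.4.1 and 4.7.1. Its size cannot be stated, because it depends on an unknown relapse share and recovery. It concerns the month-6 secondary contrasts only and justifies a statement and a supplementary analysis, no more. The change is worth making, but the trial does not stand or fall by it.

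**What to change.** 1. In section 5.3.2, analyse the month-6 value by ANCOVA with the baseline value as covariate (NT-proBNP on the log scale for both), and report the between-arm difference with its 95% CI.
2. For echo LVEF, LVEDD, NT-proBNP, heart rate and systolic and diastolic blood pressure, a mixed model for repeated measures with arm, visit, arm-by-visit and baseline may be used instead, so that retained patients missing month 6 still contribute. CMR variables and KCCQ-12 stay with ANCOVA.
3. Keep the Wilcoxon rank-sum test on the change as a sensitivity analysis.
4. State that the main analysis uses month-6 values regardless of restarted heart failure treatment (treatment policy). Add one supplementary analysis for patients who met the primary endpoint and restarted: either worst rank or the values before restart.

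No new data are needed. The cost is a modelling assumption (approximately normal residuals, eased by the log scale and checked by the Wilcoxon analysis) and some extra programming.

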## **5.4 Handling of Missing and Aberrant Data**

A statistical analysis plan will be developed before the trial begins. After database lock, statistical analyses will be conducted according to the plan, and a statistical analysis report will be generated based on the results.

**5.4.1 Handling of Missing Data:** Missing data will not be imputed; analyses will be performed using the available data.

**5.4.2 Handling of Erroneous Data:** During data management, quality control will be performed on the database. Identified erroneous data will be queried to the investigators via a data query form. Corrections will be made based on the investigators' written responses. The database will only be locked after all erroneous data have been corrected.

**5.4.3 Handling of Implausible Data:** During data management, logical checks will be performed on the database. Implausible data will be queried to the investigators via a data query form. Adjustments will be made based on the investigators' written responses. The database will only be locked after all implausible data have been resolved.

## **6. Data Management**

### **6.1 Database Establishment and Data Collection**

The trial will collect all study data using a standardized electronic data-entry system according to the protocol. All variables, form structures, and data-entry rules are predefined, and every recorded item must be verifiable against source documents. The study database will be built and maintained by trained data-management staff to ensure data quality.

### **6.2 Raw Data Verification**

Investigators will confirm that all electronically recorded data match the source documents. Any inconsistencies will trigger data queries, which site staff will resolve by checking the original records and updating the database accordingly to ensure accuracy and completeness.

### **6.3 Data Entry**

Data will be entered by two data entry personnel independently in duplicate. After consistency checks, any discrepancies will be verified and corrected. Once all data are reconciled, the database will be submitted to the data management manager for final review.

### **6.4 Preservation of Data Management Documents and Data Transfer**

The data management manager will retain all data management-related documents as required and will transfer the locked database and related materials to the statistician for statistical analysis.

## **7. Benefit and Risk Analysis**

### **7.1 Potential Benefits**

Both treatment strategies in this study have their respective advantages. Regardless of group assignment, participants will receive close monitoring by physicians, providing individualized treatment and medical guidance. The costs of CMR and echocardiography at the 6-month follow-up will be covered by the investigators for all participants.

### **7.2 Potential Risks**

Adverse events may occur during participation in this study, although they may not be related to the clinical trial. Participation may also result in no improvement in the participant's condition.

## **8. Quality Control of the Clinical Trial**

### **8.1 Training of Investigators and Research Assistants**

To ensure trial quality, all investigators and research assistants must undergo training before the trial begins. Training will cover, but is not limited to, the study protocol, adjustment of

HF medications, and recording and reporting of adverse events. Continuous training should be provided during the trial as needed. When significant updates to the protocol or related documents occur, retraining of the project team and investigator team is required. For trial personnel joining after the initiation meeting, complete training must be conducted before they engage in any trial activities. All completed trainings must be documented with signed training records.

## **8.2 Quality Control of Imaging Examinations**

To ensure the quality of echocardiography and CMR, the same sonographer and CMR physician will perform all examinations on the same equipment for each patient, minimizing bias.

## **8.3 Measures to Improve Participant Compliance**

Informed consent will be carefully implemented to ensure participants fully understand the trial requirements and cooperate with study procedures.

Investigators will provide close follow-up, monitoring symptoms, blood pressure, heart rate, medication adherence, and test results, and offer individualized medical advice. The costs of CMR and echocardiography at the 6-month follow-up will be covered by the investigators.

# **9. Ethical Considerations and Informed Consent in the Clinical Trial**

## **9.1 Ethical Considerations**

The clinical trial must comply with the Declaration of Helsinki and relevant national regulations and standards for clinical trials. The trial may only commence after approval of the study protocol by the ethics committee of the responsible clinical trial institution.

Before enrolling each participant, the investigator is responsible for providing a complete and comprehensive explanation in writing to the participant or their designated representative regarding the purpose, procedures, and potential risks of the trial. Participants must be informed of their right to withdraw from the trial at any time. For prospectively enrolled participants, a written informed consent form must be provided prior to enrollment, and the trial physician is responsible for ensuring that each participant has given informed consent before entering the study. The signed informed consent form must be retained as part of the clinical trial documentation.

If the informed consent form is revised during the trial, the revised version must first be approved by the ethics committee before implementation. Once approved, all participants whose follow-up is not yet completed must sign the revised informed consent form.

Before initiating the trial, investigators must submit the study protocol, informed consent form, and other relevant documents to the ethics committee of the hospital overseeing the

clinical trial. The trial may only begin after obtaining ethics committee approval. Any amendments to the study protocol must also be approved by the ethics committee before implementation. Serious adverse events occurring during the trial must be reported promptly in writing to the ethics committee.

## **9.2 Informed Consent Process**

For prospectively enrolled participants, investigators are responsible for providing a complete and comprehensive written explanation of the trial's purpose, procedures, and potential risks to each participant or their legal guardian before enrollment. Participants must be informed of their right to withdraw from the trial at any time, and their personal information will be kept confidential. Each participant must receive a written informed consent form prior to enrollment. Investigators are responsible for obtaining the signed informed consent form before the participant enters the study and for retaining it in the trial records.

For participants who lack decision-making capacity, enrollment is permissible if the ethics committee gives preliminary approval and the investigator determines that participation is in the participant's best interest. In such cases, the participant's legal guardian must sign and date the informed consent form before trial initiation.

If the participant or their legal guardian is unable to read, a witness must be present during the informed consent process. The informed consent form must be thoroughly explained, and the witness must confirm that the written form is consistent with the oral explanation. The participant or guardian provides verbal consent, after which the witness signs and dates the consent form. The witness's signature and the investigator's signature must be completed on the same day.

## **10. Regulations for Reporting Adverse Events**

### **10.1 Definition and Reporting of Adverse Events**

#### **10.1.1 Definition**

An adverse event (AE) is any unfavorable medical occurrence that arises during the clinical trial, regardless of whether it is related to the study.

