#### **4.4 Intervention**

The intervention group will undergo a protocol-defined, stepwise withdrawal of HF medications, while the control group will continue GDMT for HF. Apart from the intervention under investigation, the management of AF/AFL and other non-HF comorbidities will be conducted in accordance with clinical guidelines for both groups. The investigators will evaluate and manage adverse drug events appropriately, which may include dose reduction or discontinuation of the offending medication.

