#### **10.1.2 Reporting Regulations**

##### **1) Grading of Adverse Event Severity**

The severity of adverse events will be graded based on the Common Terminology Criteria for Adverse Events (CTCAE) version 5.0. The criteria for evaluating adverse events are shown in Table 11-1.

Table 10-1. Adverse Event Evaluation Criteria

| Severity Grading | Criteria                                                                                                                                                                                            |
|------------------|-----------------------------------------------------------------------------------------------------------------------------------------------------------------------------------------------------------------|
| Grade 1          | Mild; asymptomatic or minimal symptoms; only detectable clinically or by diagnostic tests; no treatment required.                                                                                               |
| Grade 2          | Moderate; requires minor, local, or non-invasive intervention; instrumental activities of daily living limited  .                                                                                   |
| Grade 3          | Severe or medically significant but not immediately life-threatening; results in hospitalization or prolongation of hospitalization; causes disability; basic activities of daily living limited  . |
| Grade 4          | Life-threatening; requires urgent intervention.                                                                                                                                                                 |
| Grade 5          | Death related to the adverse event.                                                                                                                                                                             |

Notes:

 In the criteria, “;” denotes “or.”

 Instrumental activities of daily living refer to cooking, shopping for clothes, using the telephone, managing finances, etc.

 Basic activities of daily living refer to bathing, dressing/undressing, eating, toileting, taking medications, and not being bedridden long-term.

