### b) Potential Adverse Events and Management

Potential study-related adverse events include cardiovascular death, nonfatal stroke, nonfatal myocardial infarction, heart failure–related hospitalization, acute kidney injury, and others. Physicians should manage these events symptomatically, actively investigate the cause, implement appropriate treatments, and report according to protocol.

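### Secondary endpoint (4) counts adverse drug events in an open-label trial that randomises drug exposure, so for components without a threshold the same background event could count on the drug and not after withdrawal

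*Protocol*

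**What the plan says.** - **Endpoint.** Section 4.3.2(4) reads "Adverse drug events, including symptomatic hypotension, renal dysfunction, hyperkalemia, bradycardia, diabetic ketoacidosis and urogenital infection". Item 4 of the secondary endpoints in the Protocol Summary has the same list. The list is open-ended.
- **Component definitions.** Section 4.3.2 defines three of the six named components, beginning "renal dysfunction: a decrease in the eGFR of", "hyperkalemia: serum potassium" and "bradycardia: heart rate at rest". Each is a numerical threshold (for potassium above 5.5 mmol/L, for resting heart rate below 40 beats/min), and none mentions a drug. Symptomatic hypotension, diabetic ketoacidosis and urogenital infection have no definition.
- **Other use of the term.** Section 4.4 says how investigators manage adverse drug events, "which may include dose reduction or discontinuation of the offending medication".
- **Adverse events in general.** Section 10.1.1 covers "any unfavorable medical occurrence that arises during the clinical trial, regardless of whether it is related to the study". For grading, 10.1.2 says "The severity of adverse events will be graded based on the Common Terminology Criteria for Adverse Events (CTCAE) version 5.0". Section 10 has no causality scale. Its nearest wording is a list that begins "Potential study-related adverse events include cardiovascular death, nonfatal stroke", without a rule for judging relatedness.
- **Design and test.** The trial is open-label (4.1), with 25 patients per arm (Protocol Summary). Categorical secondary endpoints are compared by chi-squared or Fisher's exact test (5.3.2).

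**The concern.** Taking or not taking the heart failure drugs is what this trial randomises. An endpoint that requires an event to be caused by a drug depends on the randomised factor twice: through any real effect of the drug, which the trial wants to measure, and through the opportunity to blame a drug, which it does not. A urinary infection unrelated to treatment can be put down to an SGLT2 inhibitor in a control patient taking one. It cannot be put down to that drug in a withdrawal patient who stopped it weeks earlier.

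The judgement would be made by staff who know the allocation. The only blinded assessor that the protocol describes is the CMR reader (4.6.2). The error would run towards the trial's rationale, since the Background presents avoidable drug side effects as a reason to withdraw treatment. At stake is the between-arm comparison of drug side effects. The primary endpoint is not affected.

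**Working it through.** There is no figure in the protocol to reproduce, so the check is first one of wording and then an illustration with assumed rates.

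**1. Which components depend on attribution?**

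| Component | Rule in 4.3.2 | Attribution needed to count? |
|---|---|---|
| Renal dysfunction | eGFR threshold from randomisation | No |
| Hyperkalemia | potassium threshold | No |
| Bradycardia | resting heart rate threshold | No |
| Symptomatic hypotension | none | Yes, read literally |
| Diabetic ketoacidosis | none | Yes, read literally |
| Urogenital infection | none | Yes, read literally |
| Unlisted events | none | Yes, read literally |

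**2. Size of the possible bias.** Assumptions:
- b is the 6-month risk of a background event not caused by the drugs, equal in both arms;
- f is the share of withdrawal-arm events that fall while a relevant drug is still being taken;
- a is the share of on-drug background events that investigators attribute to a drug.

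Controls stay on the drug throughout, so the counted risk is a x b. In the withdrawal arm it is a x b x f. The spurious difference is a x b x (1 - f), which is at most b(1 - f), reached when a = 1.

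**3. Plausible f.** Section 4.4.1 changes one drug every 2 weeks, with SGLT2 inhibitors last. Take a patient on all five classes, with beta-blocker and ARNi/RASi at full target dose and the loop diuretic and MRA at or below their thresholds. Halving from 100% to 50% to 25% and then stopping is 3 steps for each of the first two. The total is 1 + 1 + 3 + 3 + 1 = 9 steps. If the first is at week 0, the ninth is at week 8 x 2 = 16. With uniform risk over 26 weeks, f = 16/26 = 0.62, about 0.6. At the other extreme, f = 0 fits only a patient whose sole drug stops at once.

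**4. Results with a = 1.**

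| Assumed b | f = 0 | f = 0.6 |
|---|---|---|
| 4% | 4.0 points (1.0 of 25) | 0.04 x 0.4 = 1.6 points (0.4 of 25) |
| 12% | 12.0 points (3.0 of 25) | 0.12 x 0.4 = 4.8 points (1.2 of 25) |

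**5. Effect on the test.** The table gives the exact two-sided Fisher rejection probability at P <= 0.05 with 25 per arm and no true difference in event rate p. All events are counted under continuation and a share q under withdrawal.

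| p | q = 1 | q = 0.5 | q = 0 |
|---|---|---|---|
| 10% | 0.009 | 0.013 | 0.033 |
| 20% | 0.022 | 0.086 | 0.383 |

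At 10%, which lies inside the range assumed for b, the false-positive rate stays below 0.05 even at q = 0. There the harm is a biased estimate rather than a false significant result. At 20% the test is affected as well.

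**The case against.** The best reply is that the endpoint name is only a label for a list of event types. The three components that are defined count by occurrence, and vital signs, laboratory tests and Holter recordings follow the same schedule in both arms (4.5.1). On that reading there is no bias, and the counting rule could stand in a statistical analysis plan that is not shown. This reading is possible, but the text does not state it. The protocol itself chose the causal term and defined only half of the named components.

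Four stronger readings are tempting, and the documents do not support them:
- *Section 10 contradicts the endpoint.* It does not. An all-cause definition of adverse events is standard, and a narrower endpoint may stand beside it.
- *The endpoint requires an offending medication.* That phrase is in 4.4 and concerns management. It shows how the protocol uses the term, but it is not a condition of the endpoint.
- *Withdrawal patients can have no countable event.* They can: during the taper (4.4.1), after drugs are restarted (4.4.1, 4.4.3), or on substitutes such as calcium channel blockers, other glucose-lowering drugs or antiarrhythmics (4.4.3, 4.4.4). Conversely, a control patient need take only one class of heart failure drug (4.2.1, criterion 8) and may have it reduced or stopped for an adverse drug event (4.4).
- *A difference must arise by definition.* It could arise, for some components, if investigators apply the wording literally.

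It also stands that b, f and a are assumed, and that attributing every background event in controls to a drug is an extreme case.

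**Conclusion.** The point holds as a defect of wording in 4.3.2(4) and the Protocol Summary. An undefined causal term serves as a between-arm endpoint in an open-label trial of drug withdrawal. For symptomatic hypotension, diabetic ketoacidosis, urogenital infection and unlisted events, it leaves open whether attribution decides what counts. If it does, the comparison could be tilted towards withdrawal.

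The size is an upper bound under assumed rates: about 2 to 12 percentage points, or 0.4 to 3 patients of 25. Partial attribution in controls, a long taper, restarts and substitute drugs all make it smaller. Renal dysfunction, hyperkalemia and bradycardia are not affected if their thresholds are applied as written. The endpoint is secondary in a 50-patient pilot, so this should be corrected but does not threaten the main result.

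**What to change.** In 4.3.2(4) and in item 4 of the secondary endpoints in the Protocol Summary, replace the opening words before the list of components with:

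*Adverse events (as defined in 10.1.1) of the following types, counted in both groups from randomisation to 6 months irrespective of judged relation to a drug or current drug use:*

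Keep the existing thresholds. Report any investigator attribution descriptively only, outside the between-arm comparison.

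The cost is one sentence in two places. Section 10 already has all adverse events recorded, so no new data are needed and no treatment rule changes. There are three consequences to accept:
- the apparent benefit of withdrawal may be slightly smaller;
- events unrelated to any drug add some noise to the comparison;
- the list becomes closed, so unlisted event types are reported under Section 10 and not within this endpoint.
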